### Inclusion Criteria

Patients who meet the following criteria are eligible for inclusion: (1) any sex and age between 50 and 70 years and (2) symptomatic OA of the knee with mild joint discomfort for at least 6 months before enrollment, following American College of Rheumatology (ACR) criteria with history and physical examination [16] (participants diagnosed with bilateral knee OA are asked to identify the most affected knee at baseline [BL], and this knee is evaluated throughout the study period); (3) available confirmatory radiographic diagnosis (performed within the previous 6 months) with Kellgren-Lawrence score 2 at the knee joint evaluated [17]; (4) participants experienced pain for at least 15 of the 30 days before study entry; (5) signed informed consent; and (6) demonstrated compliance with all study requirements.

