### Exclusion Criteria

Patients meeting any of the following criteria are excluded from the study: (1) any inflammatory arthritic condition (other than knee OA), fibromyalgia, multiple sclerosis, or autoimmune disorder; (2) oral corticosteroid treatment within 4 weeks before screening; (3) IA injections of HA or corticosteroids in the target joint within 3 months before screening; (4) participants who have taken anti-inflammatory or chondroprotective drugs (such as chondroitin sulfate, glucosamine, methylsulfonylmethane, HA, and diacerein) within 2 weeks before selection; (5) use of HA-containing nutritional supplements or cosmetics within the month before the study; (6) previous surgical treatment of the knee joint or require OA-related surgery (such as high tibial osteotomy or arthroplasty) or have complications that require hospitalization and surgical treatment; (7) significant injury to the target joint within the 6 months before screening; (8) participants who are following an energy-restricted diet for weight loss; (9) pregnant women, nursing mothers, or women of childbearing potential who are not using adequate methods of contraception; (10) participants with cardiovascular, hepatic, renal, respiratory, or hematologic disease, or any other medical or psychiatric condition that, in the opinion of the investigator, would impair participation or is likely to result in hospitalization during the course of the study; (11) participation in an interventional clinical trial within the past 30 days; and (12) presence of any clinically significant medical condition that, in the opinion of the investigator, precludes patient enrollment in the study.

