### Intervention

All patients will receive Syalox 300 Plus (River Pharma), a food supplement containing HMWHA. Although this product has been available in European countries for several years and has been used in the clinical practice by hundreds of orthopedists, only a few clinical trials [18] have been conducted to test whether this type of product with oral HA could complement the treatment of patients affected by OA. In this study, the investigational product (IP) is administered as 1 tablet daily for 8 weeks, preferably before or during meals, with plenty of water. Following local legislation for food supplements, the product used is the same as that available in the market and must be administered as reported in the instruction for use. No changes in the dosage are planned during the study period. However, the investigator may decide to discontinue IP administration in case of adverse events (AEs) and serious AEs (SAEs) or to use other therapies at any time if he or she deems it necessary for the patient’s health. The reason for discontinuing the administration must be documented in both the source documents and CRF. At BL, each patient is given an IP package for the entire duration of the study (60 tablets). Patients are instructed to return all IP packages to the investigator at the end of the study to ensure product accountability. The IP contains 2 ingredients: HMWHA and dry extract of Boswellia.

A medical literature analysis has shown that HMWHA has been effective in relieving knee pain in various clinical trials without side effects [12,13]. The amount of HMWHA in the IP used in this study, which is greater than 2.8 million Da, is comparable to or slightly higher than that of supplements already available on the market for viscosupplementation in OA [13] and used in clinical trials [19-21].

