### Concomitant Care and Interventions

For ethical reasons, we decide to administer also rescue medications. This term [28] refers to drugs that can be administered to patients in a trial if the efficacy of IP is not satisfactory.

Two boxes of Paracetamol LPH 500 (40 tablets in total) are delivered at the BL and collected at the final visit (week 8). Each tablet contains 500 mg of paracetamol. If requested by the patient, an additional box of 20 tablets is delivered at week 4. In any case, a daily dosage of >3000 mg (6 tablets per day) is not allowed.

For the duration of the pilot study, participants are prohibited from consuming alcohol, abusing drugs, following an energy-restricted diet for weight loss, taking diuretics, or any medication listed in the exclusion criteria. Additionally, routine intake of antiresorptive drugs such as bisphosphonates or estrogen is not permitted.

There are no restrictions on treatments previously administered by the participants for clinical conditions unrelated to the study.

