**Figure 3 figure3:**
[figure not shown]
Flow diagram (CONSORT [Consolidated Standards of Reporting Trials]) of the pilot study.

**Table 1 table1:** Schedule of observation points and assessments.

Assessments	Visit 1	Visit 2	Visit 3
Days	–14 to 0	28 (±2)	56 (±4)
Weeks	–2 to 0	4	8
Informed consent	✓		
Inclusion criteria	✓		
Exclusion criteria	✓	✓	✓
Demographics and medical history	✓		
Physical examination and vital signs	✓		
Orthopedic assessment	✓		✓
Concomitant treatments	✓	✓	✓
Actigraphy—sensor delivery (1 week before the visit; optional)	✓		✓
Actigraphy—sensor return (optional)	✓		✓
KOOS^a^	✓	✓^b^	✓
VAS^c^	✓	✓^b^	✓
ROM^d^ by a goniometer	✓	✓^b^	✓
Ultrasonography	✓		✓
IP^e^ delivery	✓		
IP return			✓
Rescue medication delivery	✓		
Rescue medication return			✓
Rescue medication accountability card delivery	✓		
Rescue medication accountability card return			✓
Adverse events	✓	✓^f^	✓

^a^KOOS: Knee Injury and Osteoarthritis Outcome Score.

^b^Tests and examinations not mandatory if the visit is performed via telephone call.

^c^VAS: visual analog scale.

^d^ROM: range of motion.

^e^IP: investigational product.

^f^Safety (adverse event or serious adverse event checking) is mandatory in any case.

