### Statistical Analysis

Quantitative variables, such as demographics, are described using mean and SD if normally distributed and median and IQR if nonnormally distributed. Comparative analysis is performed using either the Student *t* test (2-tailed) or the Mann-Whitney *U* test, depending on the distribution of the variables. Factorial variance analysis can be used to evaluate interactions between quantitative variables and linear progression models to identify possible confounding bias with independent variables. Categorical variables are described using frequencies and percentages, and comparative analyses using the χ^2^ test. The Spearman rank correlation, a nonparametric test, measures the degree of association between 2 variables. The Spearman rank correlation test is appropriate for analyzing correlations when variables are measured on at least an ordinal scale, as is the case in this study. This test does not make any assumptions about the distribution of the data. When analyzing the enrolled population, we use the Spearman rank correlation test to identify any strong positive correlations (at least 0.7) between the reduction in VAS (at rest) and ultrasound parameters, as well as between the reduction in VAS (at rest) and ROM improvement.

We evaluate the quality and completeness of the collected data before conducting any analysis. If a participant is missing information for 1 or more variables, even after the queries are resolved, the missing data are not replaced. Additionally, if a participant has violated the inclusion and exclusion criteria, the corresponding data are excluded from the analysis.

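### The rule that drops eligibility violators is not limited to violations present before the first tablet, so it can remove treated patients because they worsened or were harmed

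*Protocol article*

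**What the plan says.** The last paragraph of Statistical Analysis sets the rule: "if a participant has violated the inclusion and exclusion criteria, the corresponding data are excluded from the analysis". It does not say when the violation must have occurred or which outcomes are affected, and it names no analysis that keeps all treated patients. The same section describes the correlation analysis as one of the enrolled population, which does not fit with deleting enrolled patients.

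Three other places determine how far the rule reaches:

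- **Table 1.** The row "Exclusion criteria" is ticked at Visits 1, 2 and 3, the last two being weeks 4 and 8 on treatment. The row "Inclusion criteria" is ticked at Visit 1 only.
- **Exclusion Criteria.** Criterion 6 covers patients who need surgery for their osteoarthritis or who "have complications that require hospitalization and surgical treatment". Criteria 10 and 12 cover disease that, in the investigator's opinion, would impair participation, is likely to lead to hospitalization, or precludes enrollment.
- **Concomitant Care and Interventions; Intervention.** Prohibited during the study are, among others, diuretics "or any medication listed in the exclusion criteria". Yet the investigator may stop the product "or to use other therapies at any time if he or she deems it necessary for the patient’s health".

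Under Primary Outcomes, safety is to rest on all adverse and serious adverse events. Under Secondary Outcomes, the decision to proceed to the main trial needs improvement in VAS at rest and in at least one of ROM and ultrasound. No size of improvement is given.

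**The concern.** Excluding a patient who was ineligible before treatment cannot depend on how that patient responded. Excluding a patient for something first found at week 4 or 8 can. If the knee deteriorates until surgery is needed, or an illness develops that the investigator judges incompatible with participation, the re-check can class that patient as a violator and the rule then removes the data. The patients most exposed to removal in this way are those doing badly.

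The trial has few defences against this. It has 8 patients and no control group in which the same selection would operate, and its progression decision rests on observed improvement. Safety is exposed too. Potential Risks lists severe allergic reactions, hepatic and renal impairment, thrombocytopenia and agranulocytosis among the possible harms of the study products. A patient with one of these could meet criterion 10 or 12 at the re-check, and the event would then be dropped on a literal reading.

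**Working it through.** **Step 1. The plan's own figure.** Sample Size plans 80 patients for the main trial; the Rationale sets the pilot at 10% of that. 0.10 × 80 = 8, which reproduces the stated number. Each patient removed is 1/8 = 12.5% of the sample.

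**Step 2. Which exclusion criteria can be met for the first time on treatment?**

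| Criteria | Wording | Can arise on treatment? | Possible link to outcome |
|---|---|---|---|
| 2, 3, 4, 5, 7, 11 (corticosteroids, injections, anti-inflammatory or chondroprotective drugs, HA supplements, injury, other trials) | Fixed window before entry | Not literally | – |
| 6 (need for surgery; complications) | No window for these parts | Yes | Worsening knee |
| 10, 12 (disease, investigator's opinion) | No window | Yes | Harm or intercurrent illness |
| 8, 9 (diet; pregnancy) | No window | Yes | None obvious |

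The point therefore rests on criteria 6, 10 and 12. The drug criteria concern use before entry. Later use breaches the separate prohibition in Concomitant Care and Interventions, and would count as an eligibility violation only if the Table 1 re-check is read that way.

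**Step 3. Size, as a worst case.** The plan gives no SD for the VAS change, so results are in SD units. Assumptions: 8 independent normal improvement scores with mean 0 (no true change) and SD 1, and the *k* patients removed are the *k* worst responders. For each of 500,000 simulated samples, the mean of the remaining 8 − *k* scores was taken.

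| Removed | Left | Shift in mean improvement | Chance that the mean shows improvement |
|---|---|---|---|
| 0 | 8 | 0 | 50% |
| 1 | 7 | +0.20 SD | 71% |
| 2 | 6 | +0.38 SD | 85% |
| 3 | 5 | +0.55 SD | 92% |

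With a true improvement of 0.3 SD (also assumed) the shifts are the same, and the chance goes from 80% with none removed to 92% and 97% with 1 and 2 removed.

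**Step 4. The other end of the range.** If 1 or 2 patients are removed for reasons unrelated to outcome, the shift is 0 and the chance stays at 50%.

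**Step 5. The same effect as a proportion.** If 4 of 8 patients improve (illustrative), removing 1 or 2 who did not turns 4/8 = 50% into 4/7 = 57% or 4/6 = 67%.

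**The case against.** The strongest reply is that the sentence was meant for patients found to have been ineligible at entry, and that analysis sets are often left to a statistical analysis plan, which is not shown. The Objectives section also calls the efficacy data preliminary. But the rule is stated here without that limit, and the table beside it re-checks eligibility on treatment. A reader applying the article would be entitled to delete such patients.

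Several stronger readings are tempting, and the documents do not support them:

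- *Patients who start anti-inflammatory drugs or corticosteroids are deleted.* The relevant exclusion criteria are pre-entry windows, so this is an ambiguity to reconcile, not a stated consequence.
- *Non-adherent patients are deleted.* Inclusion criterion 6 asks for "demonstrated compliance with all study requirements", which is awkward for an entry criterion. But inclusion is checked at Visit 1 only, and nothing makes later poor adherence a ground for deletion.
- *Rescue users are deleted.* Paracetamol is permitted, and its use is an exploratory outcome. Non-responders who take only paracetamol, or nothing, stay in.
- *Withdrawn patients vanish.* Missing values are not replaced, which leaves no week 8 change score but does not remove the patient's other data. Reasons for withdrawal are recorded on the CRF.
- *Adverse events will certainly be lost.* Primary Outcomes is the more specific provision and asks for all events. The two passages conflict, and a reasonable analyst might follow the safety passage.

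**Conclusion.** The concern stands as a risk that the wording creates. The rule permits deletion of treated patients for events after baseline, at least three exclusion criteria tie such deletion to worsening or harm, and a literal reading conflicts with the primary safety outcome. A reader might infer that treatment failures are removed and improvement is inflated. The documents show only that this can happen: they give neither the number of violators nor any link to outcome.

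The bias runs from zero, if violations are unrelated to outcome, to about +0.20 SD with 1 removal or +0.38 SD with 2, if those removed are the worst responders. The 71% and 85% apply to a mean VAS change above zero when there is no true effect. They are not the probability of a decision to proceed, because that decision also needs improvement in ROM or ultrasound and does not define improvement as a mean above zero. With 8 patients and no control, the upper part of this range is enough to matter.

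**What to change.** 1. Make the main analysis all enrolled patients who took at least one tablet, using all available data. Always use this set for safety.
2. Restrict eligibility exclusions to violations that existed before the first tablet, and apply them only in a secondary per-protocol analysis.
3. Beside the progression decision, report the number of violations, withdrawals and uses of prohibited therapy, with reasons. Counting such patients as not improved is not proposed, because the progression rule contains no per-patient definition of response.
4. Reword inclusion criterion 6 as able and willing to comply.
5. Reconcile Inclusion Criteria, Exclusion Criteria, Concomitant Care and Interventions, Table 1 and Statistical Analysis. State what the re-check at weeks 4 and 8 is for, and whether use of a prohibited drug on study has any consequence for the analysis.

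The cost is wording and, if the analysis has already been run, a repeat on data already collected. The Results section says treatment ended in May 2018 and full results were still to be published, so the change should be dated and described as made after data collection. The apparent improvement may become slightly less favourable.

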## Results

Recruitment and treatment of the 8 patients began on February 15, 2018, and was completed on May 25, 2018. Data analysis was planned to be completed by the end of 2018, with full results expected to be published in the last quarter of 2024.

## Discussion

### “You Have to Walk Before You Can Run”

We wanted to perform an RCT to test oral HMWHA in patients with OA. We calculated the sample size (approximately 80 evaluable participants), defined the design (double-blind randomized vs placebo), and estimated the duration of treatment (at least 4 months). We have previously conducted and published a systematic review of existing RCTs on HA [13]. We were even trusted to have found a potential problem that caused the limited and equivocal results of the previous RCT with HA published in the medical literature. We abruptly halted our planning and, gazing into each other’s eyes, reminded ourselves of the old adage: “You have to walk before you can run.” It would be unrealistic to attempt to build and execute a future main RCT to test oral HMWHA in OA with only the limited resources of a team of investigators in Eastern Europe. The risk of misplanning trial management (ie, duration of enrollment, sites to be involved, visits, and examinations) and the possibility of bias in the selection of outcomes is too high. It is not feasible to consider such a significant risk in terms of finances, time, and resources without first testing the project, even on a small scale. To ensure the feasibility of the monthly recruitment rate, to estimate the time and budget requirements for the main study, and to avoid potential bias in the selection of end points and their measurement, it is necessary to perform a preliminary evaluation. For this reason, the present pilot feasibility study protocol was designed and developed. Three additional issues related to trials of oral HA in patients with OA can be discussed.

The first is a comment reported by the principal investigator in a letter to the editor [36]. In particular, he reported several additional critical issues regarding the parameters used to measure the end points. The use of VAS for pain measurement and specific scores for OA outcomes, such as KOOS, as well as scales tested only in the Japanese population, for example, Japanese Knee Osteoarthritis Measure and Japanese Orthopaedic Association scales [37,38], should be considered a subjective measure despite being standardized and validated. In 7 trials conducted in Japan, only the VAS and/or other types of scales were used to measure OA symptoms, and no objective tools, such as ultrasound or isokinetic dynamometers, were used. These instruments were used in only 4 of 10 studies performed in Europe and America. However, several studies have generated ambiguous results when using ultrasound [39-41] and isokinetic dynamometers [40-42]. In only 2 studies, ultrasound measurements showed a statistically significant difference from the control group [39,40]. Furthermore, it is hard to define a positive result when the only statistically proven difference from the control group is the isokinetic peak torque at 240° of the extensors [37]. In 2 trials [39,41], the methods used to apply and evaluate ultrasound examinations were not reported. In the third study [40], the only ultrasound data collected was the measurement of synovial effusion in the suprapatellar recess on the longitudinal axis in millimeters following the 2005 EULAR guidelines [43]. Isokinetic tests were conducted using the Biodex System (Biodex Medical Systems), which is considered the gold standard for such measurements. However, in the study protocol, it was not considered that an increased level of synovial fluid (4 mm in the suprapatellar recess) could be a common symptom in patients with knee OA. Therefore, in several cases in the abovementioned trials, excess synovial fluid could cause pain and interfere with the isokinetic assessment of muscle strength [40]. The reason for using this tool as the primary efficacy assessment in 3 trials was that a reduction in knee OA pain could indicate an increase in work, power, and peak torque of the leg muscles. This surrogate end point could be useful for testing HA on joint pain in athletes or young people. In contrast, the studies that tested isokinetic assessment had patients with a mean (SD) age of 56.1 (8.00) years [40], 42.38 (10.16) years [41], and 59.6 (8.3) years [42]. Even if there were a statistically significant difference in muscular strength in a similar population of older patients, it would not be considered clinically important because this parameter does not affect the patients’ QoL.

None of the trial reviews objectively evaluated the composite measurement of pain and basic activities such as walking or performing daily tasks. Actigraphs, which are capable of recording these data, have been tested in clinical trials with patients with knee OA [32]. The cost of a single actigraph is approximately US $100, which is significantly less than that of the Biodex system. Additionally, actigraphs are user-friendly, and their data can be collected using a standard personal computer.

Second, ROM, another tool that can objectively measure the potential improvement in OA using a simple goniometer, paradoxically was not included as an outcome in these trials. ROM measurement remains widely used in orthopedics, and we believe that it can be easily correlated with specific scales such as VAS and KOOS to improve patient assessment. In this pilot study, because ROM is not the best way to assess disability in severe OA, we only included patients with a Kellgren-Lawrence score of 2.

The third topic is our willingness to include the daily average consumption of rescue medications as an exploratory outcome. In a similar OA population with a Kellgren-Lawrence score of 2 or 3 and treated with placebo for 24 weeks, the number of paracetamol 500 tablets used per day ranged from 0.34 [44] to 1.32 [33]. Effective medications should be the only option to reduce the need for rescue medications, so collecting and evaluating this objective parameter should be straightforward.

The criteria that we have identified for determining whether to proceed with the future RCT are improvement in both the subjective outcome (VAS at rest) and at least one of the objective outcomes at the final visit. We also believe that owing to the small sample size of this pilot study, a statistically significant correlation between objective and subjective parameters as a condition for starting the main future RCT is not required at this stage.

On the basis of the findings of this open-label pilot feasibility study, we will be able to design and conduct the future double-blind RCT to evaluate the efficacy of oral HA in knee OA. In clinical trials, investigators generally record these findings as the correlation between objective and subjective outcomes (ie, ROM and VAS, respectively). In daily medical practice, orthopedics uses the same findings (the link between the subjective symptoms reported by the patient and the objective signs of their visit) to demonstrate the patient’s improvement. Therefore, correlating objective and subjective improvements in patients affected by knee OA could provide an additional measurement tool for medical doctors in their daily orthopedic practice.

